## Abstract

**Background:**

Over the past 2 decades, the gut microbiota has emerged as a key player in human health, being involved in many different clinical contexts. Yet, many aspects of the relationship with its host are poorly documented. One obstacle is the substantial variability in wet-laboratory procedures and data processing implemented during gut microbiota studies, which poses a challenge of comparability and potential meta-analysis.

**Objective:**

The study protocol described here aimed to better understand the relationship between health, dietary habits, and the observed heterogeneity of gut microbiota composition in the general population. “Le French Gut – Le microbiote français” aimed to collect, sequence, and analyze 100,000 fecal samples from French residents using a high-quality shotgun metagenomic pipeline, complemented with comprehensive health, lifestyle, and dietary metadata.

**Methods:**

“Le French Gut – Le microbiote français” is a prospective, noninterventional French national study involving individuals, the creation of a biological collection (feces), and the exploitation of data from questionnaires and the National Health Data System (Système National des Données de Santé). This national study is open to all metropolitan French adult residents, excluding those who have undergone a colectomy or digestive stoma, or who have had a colonoscopy or taken antibiotics in the last 3 months. This is a home-based trial in which volunteers complete a questionnaire with insights about their health and habits, and in which stool samples are self-collected. Data analysis is structured into 6 work packages, each focusing on a specific aspect of the gut microbiome, including its composition and associations with lifestyle, quality of life, and health.

**Results:**

This paper outlines the study protocol, with recruitment having started in September 2022 and expected to continue until the end of December 2025. As of January 2025, a total of 20,000 participants have been enrolled. The first scientific publications based on the data analysis are expected by mid-2025.

**Conclusions:**

“Le French Gut” aims to provide a reference database and new ecosystem tools for understanding the relationship between the gut microbiota, its host, and diet. We expect to be able to find new signatures or targets and promote the design of innovative preventive strategies, personalized nutrition, and precision medicine.

**Trial Registration:**

ClinicalTrials.gov NCT05758961; https://clinicaltrials.gov/study/NCT05758961

**International Registered Report Identifier (IRRID):**

DERR1-10.2196/64894

## Introduction

### Background

The gut microbiota is composed of all the micro-organisms (archaea, bacteria, microeukaryotes, viruses, etc) that inhabit the intestine. It can be considered as an organ in its own that has coevolved with its host in a symbiotic relationship, contributing to the physiological homeostasis known as “symbiosis” [1]. The gut microbiota is a highly complex ecosystem that can be studied at different levels of resolution. This includes examining diversity parameters, characterizing enterotypes [2,3], exploring various taxonomic ranks ranging from the superkingdom to the species level, and even delving into bacterial strain–specific differences. In addition, the functional potential of the microbiota can be assessed, focusing on the metabolic and biochemical capabilities of the gut microbiome and how these are exchanged with the host.

The establishment and evolution of the intestinal microbiota throughout life is multifactorial, with the environment and dietary habits playing a major role [4-10]. Advances in research demonstrate how crucial this symbiosis is for an individual’s health and well-being [11]. Conversely, an imbalance or “dysbiosis” of the gut microbiota is associated with the risk of onset of various chronic diseases, such as those observed in intestinal and liver diseases (inflammatory bowel disease, irritable bowel syndrome, colorectal cancer, nonalcoholic fatty liver disease, and cirrhosis) [6,12,13], obesity [3,14,15], diabetes [16], autoimmune diseases [17-19] and more recently, in neurological diseases via the gut-brain axis [20-26]. Microbial alterations associated with the emergence of pathological conditions affect all microbial strata. Observed alterations include a reduction in microbial diversity [6,13,14,18,19,27], an increase in the proportion of Enterotype B2 [3], as well as disruptions across the different taxonomic ranks [6,13,16,18,19,21,23,25-27]. These alterations extend to their associated metabolic outputs, notably including a reduction in the production of short-chain fatty acids or butyrate [13,15,19,25-27].

Currently, most available microbial studies, including clinical and nutritional data in France and worldwide, are based on relatively small sample sizes, usually ranging from a few dozen to a few hundred individuals, and use different sampling and analysis methods, which makes meta-analysis complex.

To gain a better understanding of the interactions between gut microbiota, diet, and health, it is essential to significantly increase the number of samples of gut microbiota processed in a homogenous manner and cover the widest possible spectrum of phenotypes. For this reason, several large-scale initiatives have emerged, such as “The American Gut project,” launched in 2012, which involves more than 10,000 participants, and more recently the Million Microbiomes from Humans Project (MMHP), launched in 2019, which involves several countries around the world and aims to sequence 1 million metagenomes. Building on this momentum, “Le French Gut” was launched in September 2022 with the aim of describing the gut microbiota and associated nutritional and clinical data of 100,000 major individuals living in France, and the ambition to accelerate microbiota science, a source of innovation for tomorrow’s medicine and nutrition.

### Aims of the Study

By collecting 100,000 gut microbiota profiles combined with metadata on diet, health, and lifestyle, “Le French Gut – Le Microbiote Français” aims at (1) better understanding the heterogeneity of healthy gut microbiota and its link with nutrition, lifestyle, and anthropometric characteristics and (2) predicting changes in gut microbiota associated with diseases such as chronic diseases, neurodevelopmental disorders, and neurodegenerative conditions.

## Methods

### Study Design

“Le French Gut – Le Microbiote Français” is a prospective, noninterventional national study collecting human fecal samples and connecting them with data from self-filling questionnaires and from the Système National des Données de Santé (SNDS). The trial was conducted according to the recommendations of Standard Protocol Items for Clinical Trials 2013 [28]. The project aims at collecting and analyzing 100,000 stool samples from adult volunteers living in France. The duration of this inclusion phase is estimated at 5 years, and the study is planned to run for 20 years, with active (additional questionnaires) and passive follow-up thanks to its link with the SNDS. Ancillary studies could be linked to this main project during this period, including extending it to French overseas departments and territories and to minors.

The study is being carried out in the general population targeting adult volunteers. Participation in the project is free of charge and takes place exclusively via the Le French Gut website [29]. Volunteers are informed about the study through various communication campaigns (national and local media, as well as social networks; Multimedia Appendix 1) and are invited to register on the dedicated website. Questionnaires and forms can be filled in using a user-friendly web interface where all data and personal information security measures are guaranteed, in particular by hosting data in a secure sovereign Health Data Hosting (HDS) certified cloud and General Data Protection Regulation compliant. After reading the information note, volunteers are asked to sign an electronic informed consent form. This procedure generates a permanent inclusion identifier. To become a participant, volunteers must follow the participant’s journey (Figure 1). After verifying eligibility for the study, the participant is asked to complete a 53-item questionnaire about their health, lifestyle, and dietary habits (generally completed in 15 minutes as mentioned in the information note). Once the questionnaire has been completed, a stool sampling kit is automatically sent to the volunteer’s address. The volunteer collects the stool sample at home using the kit and then sends the stool sample tube to the L’Assistance Publique - Hôpitaux de Paris laboratory via regular mail using a prestamped envelope approved for biological material shipment. Once the integrity and quality of the sample have been checked, the samples are pseudonymized and sent to an INRAE (French National Research Institute for Agriculture, Food, and the Environment) laboratory for biobanking and metagenomic analysis, under a secured ISO (International Organization for Standardization) 9001 and ISO 27001 certified pipeline.

It will also be possible to supplement the basic protocol with various questionnaires within ancillary protocols, targeting either the whole population or selected subsamples according to a particular phenotype (age, gender, area of residence, health status, etc).

Participants will have access to the project’s collective scientific feedback, on the website or their personal web page, and will be kept informed of project progress via regular newsletters.

**Figure 1 figure1:**
[figure not shown]
Le French Gut’s volunteer timeline. The timeline starts with the profile registration. After filing the noninclusion form, the nonopposition form, the personal identifying form, the registered becomes a volunteer. The volunteer becomes a participant once the questionnaire has been completed and the stool sample returned to the investigation team.

### Primary Outcome

The primary outcome is to characterize the heterogeneity and diversity of the gut microbiota of individuals living in France.

The gut microbiota of participants in the “French Gut” project will be characterized by describing the presence and abundance in the samples of each gut microbial genes listed in our up-to-date gene catalog [30]. From these data, the presence and abundance of the different taxonomic ranks will be inferred, ranging from a fine granularity at species and strain level to a more “zoomed out” phylum level. The richness and diversity of the microbiome (genes and species) will be described. The functional modules, corresponding to the metabolic pathways encoded by the species detected in each sample, will be determined.

### Secondary Outcomes

The secondary outcomes are to study the variations in the gut microbiota of participants as a function of microbial profile, age, sociodemographic and anthropometric characteristics, lifestyle and eating habits, presence of known pathologies at inclusion, occurrence during follow-up of certain pathologies identified by analysis of data from health questionnaires and SNDS data.

### Recruitment

The recruitment of participants is mainly based on a direct approach with “public” communication around the project. Participants learn about the project “Le French Gut” through various communication campaigns, including social media, television, radio, national and regional newspapers, magazines, and events. Volunteers can find all the information they need to take part in the project on the website [29]. Communication also aims to raise awareness on the intestinal microbiota, its link with health, and how to care for it through diet. To this end, several communication tools and podcasts are broadcast to the general public and widely distributed on social media.

Partnerships with existing cohorts will also enable their members to take part in this project. Specific populations, such as members of associations or networks, may be included once the scientific committee has validated the interest of these targeted recruitments. Registration procedures for individuals recruited in this way will be similar to those for the general public.

### Eligibility Criteria

Le French Gut is a national contribution open to anyone meeting the eligibility criteria. Eligible individuals are adult men and women living in mainland France, with an electronically signed participation agreement. Detailed inclusion and noninclusion criteria are presented in Textbox 1. These eligibility criteria may be different in ancillary projects.

Le French Gut eligibility criteria.
**Inclusion criteria**
Adult men and women residing in mainland FranceElectronically signed consent form
**Noninclusion criteria**
Nonadult personPerson not living in FrancePersons subject to a protective measure, in particular, under guardianship or curatorship or unable to express their consentPerson underwent a colectomyPerson with a digestive stomaPerson who has not signed the consentPerson who did not answer to the inclusion questionnairePerson who did not send a compliant stool samplePerson having taken antibiotic in the 3 months before inclusionPerson who underwent a colonoscopy in the 3 months before inclusion

### Sample Size

The sample size was calculated taking into account the main objective, which is to specify the presence and the abundance of over 2500 microbial species of the digestive tract and, in particular, the number of subjects required to characterize the enterotype B2 [3]. The enterotype B2 is a fairly rare ecological configuration of the microbiota that is most frequently associated with low-grade inflammation, higher prevalence of cardiometabolic conditions, and predictive of nonresponse to a diet designed to promote weight loss. According to a power test performed on French fecal samples from the MetaCardis cohort, with a population of 100,000 individuals and an expected prevalence of enterotype B2 of 5%, we will have the statistical power needed to characterize 74% of the microbiome that makes up the enterotype B2 with an α risk of 0.05 and β risk 0.80. A total of 100,000 participants will provide sufficient statistical power to assess the link between the composition of the gut microbiota and diseases of interest, but also to assess the composition of the intestinal microbiota of asymptomatic individuals at high risk of developing a disease. Indeed, diseases of interest include type 2 diabetes (prevalence of 6.4% in 2022), heart disease (8.3%), long-term psychiatric disease (4.1%) but cancer (2.3%) [31].

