For univariate analyses, conventional statistical tests (eg, Mann-Whitney-Wilcoxon, *t* test, Kruskal-Wallis, and chi-square tests) will be used to compare microbial, dietary, sociodemographic, and clinical variables across predefined volunteer groups. *P* values will be adjusted using the Benjamini-Hochberg procedure to control the false discovery rate. Correlation analyses will be conducted to examine associations between microbial species of interest and sociodemographic, lifestyle, environmental, nutritional, and clinical parameters.

Multivariate analyses will serve both descriptive and predictive purposes. Descriptive multivariate methods such as principal component analysis, factorial correspondence analysis, clustering, multidimensional scaling, and bacterial co-occurrence network analyses will be used to structure and synthesize the data. Specific complexity-reduction approaches include enterotype classification, which discretizes microbial heterogeneity into a limited number of states [2], and microbial guilds, which identify clusters of species with coabundance patterns across conditions. In addition, unsupervised clustering methods will be used to define microbiome-based subpopulations independently of phenotypic characteristics, allowing unbiased subgroup discovery.

For predictive modeling, supervised learning techniques such as discriminant analysis, random forests, and regression models will be applied to assess the microbiome’s ability to predict phenotypes of interest, including disease presence, nutritional profiles, environmental exposures, and health trajectories. These models will be trained and validated using independent test subsets to evaluate their predictive performance.

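### The sample-size statement gives a β risk of 0.80, which by definition is 20% power and contradicts the adequate power claimed in the same sentence

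*Protocol article*

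**What the plan says.** The Sample Size section of the protocol article ties the recruitment target to the description of enterotype B2. The source is given as follows: "According to a power test performed on French fecal samples from the MetaCardis cohort". With 100,000 individuals and an expected B2 prevalence of 5%, the article states that the study will have the power needed to "characterize 74% of the microbiome that makes up the enterotype B2 with an α risk of 0.05 and β risk 0.80".

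No other place in the article gives a numerical power or β. Later in the same section, power to study diseases of interest is called sufficient, with prevalences but no power figure. The Statistical Methods section and the Anticipated Findings part of the Discussion refer to the study's statistical power in words only.

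**The concern.** The sentence names two error risks side by side, α and β. The α risk of 0.05 is the usual type I error. The β risk, read the same way, is the type II error, and 0.80 is then an 80% chance of missing a true effect. A calculation with that property does not deliver the power needed to characterize anything, so the sentence contradicts itself.

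What is at stake is whether the sample-size justification can be read at all. The 74% is the stated yield of enrolling 100,000 people, and its meaning depends on the power at which it was computed. From the printed sentence a reader cannot tell whether the figure belongs to 80% or to 20% power, and nothing else in the article settles it.

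**Working it through.** **Inputs, all from Sample Size:** total N = 100,000; expected B2 prevalence 5%; "α risk of 0.05 and β risk 0.80"; stated yield 74%. The species-level effect sizes, variances, test and sidedness are not given.

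**Step 1: the plan's own figure.** The 74% cannot be reproduced, because the inputs it depends on are not in the article. Only the consistency of the error rates with the claim can be checked.

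**Step 2: the identity.** Power = 1 − β.

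- As printed: 1 − 0.80 = 0.20.
- If 0.80 was meant as power: β = 1 − 0.80 = 0.20.

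The identity does not involve the test, its sidedness or any adjustment of α, so no choice among these rescues the printed figure.

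**Step 3: why the two readings are not interchangeable (illustration only).** Assume a two-group comparison of standardised means, two-sided α 0.05 and a normal approximation. None of this is stated in the article.

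- Group sizes: 100,000 × 0.05 = 5,000 with B2 and 100,000 − 5,000 = 95,000 without.
- Standard error: √(1/5,000 + 1/95,000) = 0.0145.
- At 80% power: (1.960 + 0.842) × 0.0145 = 2.802 × 0.0145 = 0.041.
- At 20% power: (1.960 − 0.842) × 0.0145 = 1.118 × 0.0145 = 0.016.
- Ratio of detectable differences: 2.802 / 1.118 = 2.51. For a fixed effect, 80% power needs 2.51² ≈ 6.3 times the N that 20% power needs.

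**Step 4: direction of any change in the 74%.** Take the 74% to be the share of B2 features that reach the target power; this is an assumption about what it means. Every feature with at least 80% power also has at least 20% power, but not the reverse. A 74% computed at 20% power would therefore fall if the target were raised to 80%. The size of the fall depends on how the feature effects are distributed, and the documents do not give that distribution.

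**The case against.** The strongest reply is that this is a slip of the pen. The conventional power is 0.80, the sentence asserts adequate power, and nothing in the article suggests that anyone planned for a β of 0.80. The study is also noninterventional and exploratory, and no pass-or-fail test hangs on this number. If the slip is all there is, no design element or analysis changes. All of that stands, and it makes the labelling slip the likelier reading. It does not make the printed figure right, and no other part of the article corrects it.

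Three stronger readings are tempting, and the documents do not support them.

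- A reader might infer that the study really has 20% power, or that 100,000 is too few. The sentence shows only that the figure is misstated.
- A reader might infer a specific lower value for the 74% by assuming some distribution of effects. With no effects, variances or test in the article, any such value would come from the assumption rather than the plan.
- A reader might infer that α 0.05 clashes with the Statistical Methods section, where P "values will be adjusted using the Benjamini-Hochberg procedure to control the false discovery rate". Sample Size does not say whether its 0.05 is nominal or applied to adjusted P values. An article commonly leaves that detail to the full protocol, so no inconsistency is shown.

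**Conclusion.** Wrong as written. A β risk of 0.80 is 20% power, and this contradicts the power claimed in the same sentence. That conclusion rests on the definition of β alone and needs no assumption. It matters because the sentence holds the only numerical power figure offered for 100,000 participants.

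The probable correction is to the label (power 0.80, β 0.20), in which case the 74% and the target stand unchanged. The less likely possibility, that 0.80 was used as β, would make the 74% too high for 80% power by an amount that cannot be derived here. The 2.5-fold and 6.3-fold figures show only how far apart the two readings are under an assumed model. They do not estimate a shortfall in this study.

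**What to change.** Check the original MetaCardis power test to see which value was used.

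- If 0.80 was the power, replace the β statement in Sample Size with *power 0.80 (β risk 0.20)* and leave the 74% as it is.
- If 0.80 was used as β, recompute the 74% at 80% power and restate both the percentage and the error rates.

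The first case costs one corrected sentence. The second costs a rerun of the existing power calculation as well. Neither requires a change to recruitment, data collection or the analysis methods.

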### Ethical Considerations

#### Human Subject Ethics Review Approvals or Exemptions

This study has been approved by the the “Comité de Protection des Personnes” Sud-Est IV (CPP, 21.00225.000006) and the “Commission Nationale Informatique et Liberté” (CNIL, DR-2022-141).The study registered in France under reference 2021-A01439-32 was authorised on October 15,2021. Detailed trial registration dataset is presented in Multimedia Appendix 2.

#### Informed Consent

All participants were asked for their consent to participate in this study before enrollment and agree to its privacy policy and terms of service required for the remote collection of their information. The participation is entirely voluntary. Electronic informed consent form to participate is obtained from all study participants. Participants can opt out of the study anytime by going on its account. The participant may withdraw from the study at any time without justification (under the “management of my participation” section in his personal space). The participant is aware that the withdrawal will not affect any activities conducted or the use of data obtained based on the informed consent given before the withdrawal, in accordance with the Public Health Code. Furthermore, the participant consents to the reuse of his data under pseudonymized in the case of a study extension, or for ancillary studies within the same research field (microbiota), and only after approval of relevant authorities.

Participants have access to all studies in which their data have been used, and can withdraw their participation at any time from any study.

